For the analysis, the cut-points defining the control of each risk factor will be taken from the European Guidelines on CVD prevention [39]. For estimates of dyslipidemia control based on LDL, HDL cholesterol and triglycerides, we will use the cut-points agreed in the consensus statement from the American Diabetes Association and the American College of Cardiology Foundation [40].

The initial immunosuppressive regimen of the patients and changes in treatment during follow-up will be recorded. Dosage of immunosuppressive drugs will also be registered after transplantation at week 1, week 2, months 1, 3 and 6, and yearly thereafter. The use of antihypertensive and lipid-lowering drugs after transplantation will also be registered at the same times.

Post-transplant cardiovascular events are defined as the presence of myocardial infarction, invasive coronary artery therapy, cerebral vascular events (stroke and transient ischemic attacks), new-onset angina, congestive heart failure, rhythm disturbances (ventricular tachycardia, atrial fibrillation and the need for a pacemaker), and peripheral vascular disease. Peripheral vascular disease is defined as the need for invasive therapy or conservatively managed limb gangrene.

Patients will be followed-up from the date of renal transplantation until death or their return to dialysis.

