### Quantification of cardiovascular risk

Four established cardiovascular risk scores will be applied to the kidney transplant recipients at the time of transplantation: the Framingham risk factor score, the European Systematic Coronary Risk Evaluation (SCORE) equation, and two coronary risk equations that use the calibrated Framingham functions for the Spanish population, the REGICOR (Registre Gironí del COR (Gerona Heart Registry)) and DORICA (Dyslipidemia, Obesity, and Cardiovascular Risk) functions.

The Framingham risk score will be calculated using both the classic Framingham-Anderson equation [30] and the equation modified by Wilson [31]. These scores predict the risk of developing fatal or non-fatal coronary heart disease (CHD) within a 10-year time period in adults between the ages of 30-74 with no known previous history of CHD, stroke, or peripheral vascular disease. CHD includes angina pectoris, myocardial infarction, coronary insufficiency (unstable angina) and coronary heart death.

The original Framingham-Anderson equation includes the following risk factors: age, sex, systolic blood pressure, total cholesterol, HDL-cholesterol, diabetic status, tobacco smoking status and evidence of left ventricular hypertrophy on resting electrocardiogram (ECG). The Framingham-Wilson equation replaces the continuous measurements of systolic blood pressure, total cholesterol and HDL-cholesterol with categorical variables based on the risk categories of the Joint National Committee on Blood Pressure and the National Cholesterol Education Program (NCEP) [41-43]. It also takes into account information regarding diastolic and LDL-cholesterol levels, and does not include the diagnosis of left ventricular hypertrophy due to its high association with hypertension and the absence of standard, universally accepted ECG criteria.

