The European SCORE was developed by the European Society of Cardiology in 2003 as an estimation of 10-year risk of fatal cardiovascular disease (CVD) in subjects between the ages of 24 and 80. The variables used to calculate this score include age, gender, total cholesterol, systolic blood pressure and current smoking status [33]. The main difference between the SCORE risk chart and the Framingham model is that it estimates the risk for all atherothrombotic cardiovascular manifestations, including stroke, heart failure, peripheral arterial insufficiency or certain aneurysms, and not just CHD. The SCORE charts are currently the CVD charts recommended by the European Societies [44] and the Spanish Interdisciplinary Committee for Cardiovascular Disease Prevention (CEIPC) [45]. The SCORE risk charts calibrated for Spain will be used [46].

Finally, the REGICOR [32] and the DORICA [34] charts are adaptations of the Framingham equation to the Spanish population characteristics. Like the Framingham equation, these functions estimate the risk of coronary mortality and morbidity using information about age, gender, total cholesterol, HDL-cholesterol, systolic and diastolic blood pressure and smoking habits, differentiating diabetic from non-diabetic patients.

Patients will be classified as high-risk patients when their ten-year risk of coronary heart disease is ≥20% according to Framingham [31], REGICOR [32] and DORICA [34] equations or when their ten-year risk of cardiovascular mortality is ≥5% according to the SCORE system [44].

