### Statistical analysis

A descriptive analysis of the variables recorded will be performed. Observed frequencies and percentages will be used for qualitative variables, with their 95% confidence interval, and the mean and standard deviation or median and interquartilic range for quantitative variables.

The primary outcome for this study will be the estimation of the probability of cardiovascular disease in the presence of other competitive events in renal transplant patients. The cumulative incidence of cardiovascular events after kidney transplantation will be analyzed by competing risk survival methods, where each subject is at risk of failure from different causes. Therefore, each patient will be classified in four states of interest (alive with functioning graft, death, graft failure and cardiovascular disease).

Cumulative incidence functions will be used to compare the observed incidence of events between groups [48]. The cumulative incidence function regression model of Fine and Gray will be used for multiple regression analyses [49]. Additionally, the clinical relevance of different variables will be evaluated using the ARR (Absolute Risk Reduction), RRR (Relative Risk Reduction) and NNT (Number Needed to Treat).

In order to analyze the ability of each of the four cardiovascular risk scores to predict cardiovascular events rates, the concordance c index [50] and the area under the receiver-operating characteristic (ROC) curves, using a time-dependent approach [51], will be calculated. To calibrate the scores, relative risk ratios for observed-to-predicted event rates will be computed, and the Hosmer-Lemeshow test will be applied.

Based on the competing risks analysis, a nomogram to estimate the probability of cardiovascular events after kidney transplantation will be developed. The objective is to use the conditional cumulative incidence function to provide a patient-specific prediction of the probability of failure in the setting of competing risks.

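### The risk scores are calibrated against a broad cardiovascular composite that none of them predicts, so the observed-to-predicted ratio mixes endpoint mismatch with miscalibration

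*Protocol article*

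**What the plan says.** **What the scores predict** (Protocol article, Quantification of cardiovascular risk). On the two Framingham equations: "These scores predict the risk of developing fatal or non-fatal coronary heart disease (CHD) within a 10-year time period". The endpoint is spelled out: "CHD includes angina pectoris, myocardial infarction, coronary insufficiency (unstable angina) and coronary heart death". They apply "in adults between the ages of 30-74 with no known previous history of CHD, stroke, or peripheral vascular disease". On REGICOR and DORICA: "these functions estimate the risk of coronary mortality and morbidity". The high-risk cut-off for all of these is a ten-year coronary risk of 20%. SCORE estimates "10-year risk of fatal cardiovascular disease (CVD) in subjects between the ages of 24 and 80", and its cut-off is a ten-year cardiovascular mortality of 5%.

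**What is observed** (Measurements). The only outcome definition opens: "Post-transplant cardiovascular events are defined as the presence of myocardial infarction, invasive coronary artery therapy, cerebral vascular events". It goes on to new angina, heart failure, ventricular tachycardia, atrial fibrillation, pacemaker need and peripheral vascular disease. No coronary or cardiovascular death is listed. In Statistical analysis, death is a state of its own, separate from cardiovascular disease and from graft failure.

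**How the two are set against each other** (Statistical analysis). Each score's ability to predict cardiovascular events is assessed by c index and time-dependent ROC area. For calibration, "relative risk ratios for observed-to-predicted event rates will be computed", followed by a Hosmer-Lemeshow test. The Abstract and the objectives in Background name the same target. No score is given an outcome of its own.

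**The concern.** Calibration asks whether the predicted level of risk agrees with the observed level. That question has an answer only if both refer to the same event over the same period. Here the prediction is of coronary disease or cardiovascular death, and the observation is of a composite containing many events that the scores were never meant to count.

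A coronary score could be exactly right about coronary disease and still appear to underestimate, because strokes, heart failure, arrhythmias and limb events enter the numerator and not the denominator. The Hosmer-Lemeshow test compares observed with expected counts within risk groups, so the same mismatch enters every group.

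The Background already reports that Framingham underestimates event rates in renal transplant recipients. A ratio above 1 would be read as confirming this, whether or not it was true. Validation of the existing scores is one of the three main objectives in Background (a secondary objective in the Abstract), and this analysis would not answer its calibration part.

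**Working it through.** The article states no observed-to-predicted ratio, so there is none to reproduce. Its one computed figure, n = 1755, does reproduce: 386.04 events / 0.22 = 1754.7. It does not depend on this point.

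**1. Endpoints side by side**

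| Score | Predicts | In the composite but not predicted | Predicted but not listed in the composite |
|---|---|---|---|
| Framingham (both), REGICOR, DORICA | Ten-year coronary disease, fatal or not | Stroke, TIA, heart failure, arrhythmia or pacemaker, peripheral vascular disease | Coronary death |
| SCORE | Ten-year cardiovascular death | All non-fatal events | Cardiovascular death |

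**2. Size of the effect for a coronary score**

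Let s be the risk of the score's own endpoint divided by the risk of the composite, and k the predicted risk divided by the true risk of the own endpoint (k = 1 means perfectly calibrated). Then

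O/P = 1 / (s × k).

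The article gives neither s nor k, so both are assumed. With k = 1:

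| s | 0.8 | 0.7 | 0.5 | 0.3 | 0.2 |
|---|---|---|---|---|---|
| O/P | 1.25 | 1.43 | 2.0 | 3.33 | 5.0 |

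With matched endpoint and horizon, s = 1 and O/P = 1.0, as it should be.

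**3. Why a ratio above 1 is not assured**

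- *Over-prediction.* s = 0.5, k = 2 gives 1/(0.5 × 2) = 1.0. s = 0.7, k = 1.5 gives 0.95. s = 0.7, k = 2 gives 0.71. In the first case a score that doubles the true coronary risk would look perfectly calibrated.
- *Deaths outside the composite.* Write s = a + d, where a is the part of the own endpoint inside the composite and d is the fatal part outside it, both as fractions of composite risk. With k = 1: a = 0.5, d = 0.2 gives 1/0.7 = 1.43; a = 0.7, d = 0.3 gives 1/1.0 = 1.0; a = 0.7, d = 0.5 gives 1/1.2 = 0.83.
- *Competing events and horizon.* The Sample size section gives a five-year CVD incidence of 22.2%. At constant hazard with no competing events (an assumption), h = −ln(0.778)/5 = 0.0502 per year, and the ten-year risk is 1 − 0.778² = 39.5%. With an assumed competing hazard c, the ten-year cumulative incidence is h/(h + c) × [1 − exp(−10(h + c))]: 34.5% at c = 0.03 and 28.1% at c = 0.08. The observed figure therefore also depends on the horizon and on how death and graft loss are handled.

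**4. SCORE**

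SCORE predicts only deaths. The composite lists none, and death is a separate state. A fatal infarction or stroke might enter through its component, but the article does not say so. Numerator and denominator may have little in common, so no value of the ratio can be read as good or poor calibration. Nor can it be ranked against the coronary scores, whose s is different.

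**The case against.** **This is a condensed article.** Score-specific outcomes and time points may be set in a fuller plan, and the authors clearly know the differences, since they describe each endpoint and set separate cut-offs. That holds for the horizon, which the article simply does not carry into the calibration sentence. It does not hold for the outcome. The Abstract, the objectives and Statistical analysis consistently make cardiovascular events the target, and that term has one definition.

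**SCORE is broader than coronary disease.** The article does say that it covers stroke, heart failure and peripheral arterial disease. The same paragraph limits it to fatal disease, so this does not close the gap.

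**Much of the plan is untouched.** This stands. Discrimination depends on ranking, so the c index and ROC area can be computed on the composite. Framingham, REGICOR and DORICA share a coronary endpoint and can be compared with one another. The nomogram predicts the composite and is calibrated against it.

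**Stronger readings that a reader might infer, and that the documents do not support:**

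- *That the ratio must exceed 1.* The composite does not contain everything the scores predict, a score may over-predict, and competing events lower the observed rate.
- *That SCORE's ratio is at least 22.2/5 = 4.4.* The 5% is a lower cut-off for high risk, neither a mean nor a maximum. Mean predictions of 10%, 20% or 30% would give 2.2, 1.1 or 0.74. The division also sets a five-year figure against a ten-year one, and the article does not show that the 22.2% used this composite.
- *That the case for a new score would rest on an artefact.* Background bases that case on earlier studies and on transplant-specific factors, and no step of the nomogram's development depends on the ratio.

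**Conclusion.** The concern holds in this form: followed as written, the calibration analysis compares predictions of one endpoint with observations of another, and its ratio and test cannot separate endpoint mismatch from miscalibration.

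For the coronary scores the bias is generally upward, by a factor of about 1/s for a score that is right about its own endpoint. That is 1.25 to 2.0 for s between 0.8 and 0.5. The range of s is an assumption, and over-prediction, deaths outside the composite or competing events can bring the ratio to 1 or below. For SCORE the ratio is uninterpretable and not comparable with the others.

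The damage is confined to the calibration part of the score-validation objective. It should be settled before any ratio is reported, because the likely direction agrees with what the Background already expects to find.

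**What to change.** In Statistical analysis, replace the single calibration target with the following:

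- **Own endpoint, ten years.** Both Framingham equations, REGICOR and DORICA against coronary disease as the article defines it, including coronary death. SCORE against cardiovascular death.
- **Own population.** Framingham in recipients within its stated age range and without the prior disease it excludes, and SCORE within its stated age range. The article gives no separate limits for REGICOR and DORICA, so these should be written in.
- **Observed risk under competing risks.** Estimate observed ten-year risk by cumulative incidence, with other deaths and graft failure as competing events, and use it in the ratios and in any grouped comparison.
- **Composite for discrimination.** Keep the c index and ROC area on the composite. If a composite observed-to-predicted ratio is also shown, label it as not a test of calibration.

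The cost is modest. The non-fatal components are already named individually in the event definition, so most of the work is recoding, but cause of death must be coded. Each score will have fewer events and fewer eligible patients, so intervals will be wider, most of all for SCORE if cardiovascular deaths are few.

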The predictive performance of the nomogram will be evaluated by assessing both discrimination and calibration values [52]. A bootstrap re-sampling approach with 1000 replications will be used to reduce overfit bias. Discrimination will be quantified with the concordance c index and the area under the receiving operating characteristic (ROC) curve [50,51]. The nomogram will then be calibrated graphically, comparing the predicted probabilities with the actual rate of patients with cardiovascular events. A Loess curve will be fitted to the data and compared with an ideal fit. In addition, the Brier score will be calculated as a measure of the predictive accuracy of the model.

A p-value of < 0.05 will be considered as statistically significant (two-sided). Statistical analyses will be carried out with SPSS version 17.0 (SPSS Inc., Chicago, IL.) and R version 2.9.1 (The R Foundation for Statistical Computing), adding the ROCR, Design and Hmisc libraries.

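### Calibration is planned with tools that need every patient's status at the horizon, and no censoring-aware version is named, so 10-year observed-to-predicted ratios can be biased by early censoring

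*Protocol article*

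**What the plan says.** All of this is in the Protocol article, Statistical analysis, unless noted.

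- **Target.** The primary outcome is the probability of cardiovascular disease when death and graft failure compete with it. The nomogram is meant to "use the conditional cumulative incidence function to provide a patient-specific prediction of the probability of failure in the setting of competing risks".
- **Four established scores.** For calibration, "relative risk ratios for observed-to-predicted event rates will be computed, and the Hosmer-Lemeshow test will be applied". Quantification of cardiovascular risk gives these scores a 10-year horizon.
- **Nomogram.** Calibration is graphical, by "comparing the predicted probabilities with the actual rate of patients with cardiovascular events". A smoother is then added to that plot: "A Loess curve will be fitted to the data and compared with an ideal fit". As an overall measure, "the Brier score will be calculated as a measure of the predictive accuracy of the model". No horizon is given for the nomogram.
- **Censoring.** A method suited to follow-up time is named for discrimination only: the ROC area, "using a time-dependent approach [51], will be calculated". The text on calibration neither says how patients censored before the horizon are handled nor says that they are ignored.
- **Follow-up.** Design and study population takes transplants from the start of 1981 to the end of 2008. Measurements follows patients to death or return to dialysis. No calendar date for closing the data is given.

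**The concern.** The Hosmer-Lemeshow test compares counts of patients with and without the event in groups of predicted risk. A Loess curve through event status and an unweighted Brier score likewise need a yes or no for each patient at the horizon. A patient transplanted in 2005 and still event-free when the data close has no known 10-year status. To use these tools as they stand, such patients must be counted as event-free, which lowers the observed risk, or dropped, which raises it because short-follow-up patients then stay in only if something happened to them.

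Calibration carries the second objective (do the existing scores work in transplant recipients?) and part of the third (is the new score valid?). The Background says that the Framingham score underestimates events in these patients. Counting censored patients as event-free would hide part of that shortfall; dropping them would exaggerate it.

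**Working it through.** **The plan's own figure.** The one figure that can be recomputed is the sample size, with relative risk 1.33, exposure 50%, censoring 78%, two-sided α 0.05 and power 80%. Events = (1.960 + 0.842)² / (0.25 × (ln 1.33)²) = 386.04, and 386.04 / 0.22 = 1754.7, so 1755 as stated. It is not in dispute.

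**Inputs from the document.** Accrual 1981–2008 (28 years); 10-year scores; 5-year incidence of cardiovascular disease 22.2%; 1794 patients.

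**Assumptions.** Uniform accrual; data closing at the start of 2009 or of 2011; constant hazards; competing hazard (death or graft failure) g of 3% to 8% per year; 22.2% read as a cumulative incidence of the planned composite.

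**Step 1: who cannot reach 10 years.** 10/28 = 36% if data close at the start of 2009; 8/28 = 29% at the start of 2011.

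**Step 2: closed form at g = 0.05, one common risk.** CIF(t) = h/(h+g) × (1 − exp(−(h+g)t)). Setting CIF(5) = 0.222 gives h = 0.0574 and h+g = 0.1074. Then CIF(10) = 0.534 × (1 − exp(−1.074)) = 0.352. A correct model predicts this value.

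Data closing at the start of 2009:
- Counted as event-free: (18/28) × 0.352 + (1/28) × ∫₀¹⁰ CIF(c) dc = 0.226 + 2.068/28 = 0.300. O/E = 0.300/0.352 = 0.85.
- Censored before 10 years: (1/28) × (1 − exp(−1.074))/0.1074 = 6.13/28 = 0.219.
- Dropped: 0.300/0.781 = 0.384. O/E = 1.09.

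Data closing at the start of 2011:
- Counted as event-free: (20/28) × 0.352 + 1.961/28 = 0.321. O/E = 0.91.
- Censored before 10 years: (6.13 − 1.80)/28 = 0.155.
- Dropped: 0.321/0.845 = 0.380. O/E = 1.08.

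**Step 3: simulation with varied risk.** 1794 patients, standard deviation of log risk 0.6 (assumed), mean 5-year incidence 22.2%, g from 0.03 to 0.08, 300 runs per setting, predictions equal to the truth. Hosmer-Lemeshow used 10 groups and 10 degrees of freedom because the predictions are fixed. The simulation error of a rejection rate is at most √(0.25/300), about 3 percentage points. HL is the share of runs rejected at 5%.

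| Horizon | Data close | Event-free: O/E | HL | Dropped: O/E | HL |
|---|---|---|---|---|---|
| 10 y | start 2009 | 0.85–0.87 | 83–97% | 1.06–1.10 | 14–49% |
| 10 y | start 2011 | 0.91–0.92 | 29–49% | 1.05–1.09 | 15–43% |
| 5 y | start 2009 | 0.92–0.93 | 14–18% | 1.05–1.06 | 10–15% |
| 5 y | start 2011 | 0.97–0.98 | 3–8% | 1.04–1.05 | 8–11% |

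The dropped ratios are slightly below the closed form because the retained patients have somewhat higher predicted risk than the whole cohort.

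**Step 4: which feature is to blame.** With competing events but no censoring, O/E is 0.996–1.003 and rejection 4–9%. Death and graft failure before a cardiovascular event are known non-events for a cumulative incidence. Censoring causes the bias.

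**Step 5: does the remedy work?** With observed risk taken as the Aalen-Johansen cumulative incidence, O/E is 0.995–1.003 in every setting.

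**Sensitivity.** If 22.2% is instead read as one minus Kaplan-Meier, h = −ln(0.778)/5 = 0.0502. With g = 0.06, CIF(10) = 0.304 and the event-free proportions are 0.260 and 0.278, so O/E is 0.85 and 0.91. The ratios barely depend on this choice.

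**The case against.** The best defence is that the article is condensed and never says that censored patients count as event-free. The observed rate could be a cumulative-incidence estimate; the same section uses cumulative incidence functions to compare observed incidence between groups. The Loess curve is fitted to unspecified data, and the Brier score may be a weighted one. This stands in part. It rules out saying that the plan will produce a biased result, and silence on such details would not by itself be a finding. It does not cover the Hosmer-Lemeshow test, a specific method that in standard form does not accept censored outcomes and that is applied to 10-year scores.

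Three further points stand:

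- Binary tools remain usable if the analysis is restricted to patients whose potential follow-up reaches the horizon. In the simulation this gave O/E 0.996–1.003 and Hosmer-Lemeshow rejection of 2–6%. It keeps only 64% to 71% of the cohort under uniform accrual, and the article does not plan it.
- The 10-year figures describe the existing scores. The nomogram has no stated horizon, and at 5 years with later follow-up the distortion is small.
- A time-dependent ROC is already planned, so the gap concerns calibration and the Brier score.

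A reader might also infer that observed risk will be a Kaplan-Meier estimate, which would overstate incidence. Nothing proposes this, and the Discussion argues against that method.

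**Conclusion.** The concern holds in conditional form. The named calibration tools do not in standard form fit a censored outcome, and no censoring-aware version is named for them. Used at 10 years with censored patients counted as event-free, they would make a correct model look as if it overpredicts by roughly a tenth or more (O/E about 0.85 to 0.92). With those patients dropped, it would seem to underpredict (about 1.05 to 1.10). At 5 years, counting them as event-free gives about 0.92 to 0.98. These sizes rest on the assumed accrual, closing date, hazards and spread of risk.

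A reader might infer that even a perfect model is bound to look miscalibrated, or that competing events are to blame. The document supports neither: it does not fix how censored patients are treated, and competing events without censoring leave calibration intact. This should be put right before the calibration analysis; it does not affect the sample size or the cumulative-incidence analysis.

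**What to change.** 1. State the prediction horizon: 10 years for the four scores, and a named horizon for the nomogram. State the calendar date on which the data close.
2. Within groups of predicted risk, estimate observed risk by the Aalen-Johansen cumulative incidence at that horizon, with death and graft failure as competing events. Report O/E with 95% confidence intervals in place of the standard Hosmer-Lemeshow test.
3. Fit the nomogram's Loess curve to pseudo-values of the cumulative incidence at the stated horizon.
4. Use a Brier score weighted for censoring at the same horizon.

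The cost is a few sentences in the plan and slightly more analysis code. No new data are needed.
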